# Adjuvant rituximab, a potential treatment for the young patient with Graves’ hyperthyroidism (RiGD): study protocol for a single-arm, single-stage, phase II trial

**DOI:** 10.1136/bmjopen-2018-024705

**Published:** 2019-01-21

**Keywords:** thyroid disease, immunology, paediatric endocrinology, clinical trials

## Abstract

**Introduction:**

Graves’ disease (Graves’ hyperthyroidism) is a challenging condition for the young person and their family. The excess thyroid hormone generated by autoimmune stimulation of the thyroid stimulating hormone receptor on the thyroid gland can have a profound impact on well-being. Managing the young person with Graves’ hyperthyroidism is more difficult than in older people because the side effects of conventional treatment are more significant in this age group and because the disease tends not to resolve spontaneously in the short to medium term. New immunomodulatory agents are available and the anti-B cell monoclonal antibody rituximab is of particular interest because it targets cells that manufacture the antibodies that stimulate the thyroid gland in Graves’.

**Methods and analysis:**

The trial aims to establish whether the combination of a single dose of rituximab (500 mg) and a 12-month course of antithyroid drug (usually carbimazole) can result in a meaningful increase in the proportion of patients in remission at 2 years, the primary endpoint. A single-stage, phase II A’Hern design is used. 27 patients aged 12–20 years with newly presenting Graves’ hyperthyroidism will be recruited. Markers of immune function, including lymphocyte numbers and antibody levels (total and specific), will be collected regularly throughout the trial.

**Discussion:**

The trial will determine whether the immunomodulatory medication, rituximab, will facilitate remission above and beyond that observed with antithyroid drug alone. A meaningful increase in the expected proportion of young patients entering remission when managed according to the trial protocol will justify consideration of a phase III trial.

Ethics and dissemination The trial has received a favourable ethical opinion (North East - Tyne and Wear South Research Ethics Committee, reference 16/NE/0253, EudraCT number 2016-000209-35). The results of this trial will be distributed at international endocrine meetings, in the peer-reviewed literature and via patient support groups.

**Trial registration number:**

ISRCTN20381716.

Strengths and limitations of this studyThis is a group of patients in whom current therapy does not usually result in disease resolution, with only 20%–30% remitting after a 2-year course of antithyroid drug treatment with carbimazole; hence there is a significant unmet need.The behaviour of the disease in the young patient with Graves’ hyperthyroidism in terms of likelihood of remission following antithyroid (thionamide) drug is consistent between reported studies This will help us to comment on the potential impact of the trial intervention in this exploratory trial without studying a large number of patients.We will be looking at a range of markers of immune function which may help to establish some of the factors that predict response to intervention in this group of patients.It is possible that there is an immunomodulatory effect of rituximab that will not be detected because the trial duration of 2 years is too short.The likelihood of remission may be different in a 12-year-old patient with Graves’ hyperthyroidism versus a 20-year-old patient, and this consideration has not been factored into the trial design.

## Introduction

Graves’ hyperthyroidism, an autoimmune disorder, has an annual incidence of 1 in 10 000 adolescents (~700 per year) in the UK.^1^ The standard first-line treatment is the antithyroid drug (ATD) carbimazole (CBZ), which prevents the thyroid gland from manufacturing thyroid hormone and has an immunomodulatory effect.^2^ While CBZ will render most patients biochemically euthyroid in appropriate doses, only 50% of adults will remit following a standard 2-year course of ATD. The proportion of children and adolescents entering remission is considerably smaller at around 25%, and yet the side effects of CBZ are more prevalent in the young, with 20% experiencing adverse events that range from relatively minor problems such as rashes through to potentially life-threatening agranulocytosis.^3 4^ Establishing a euthyroid state can be difficult in the growing person, made more difficult by poor medication concordance in some young people.^5 6^ Avoiding relapse close to key life events such as examinations can result in prolonged courses of ATD therapy. Most young people will ultimately require thyroid gland excision (total thyroidectomy) or thyroid gland ablation with radioiodine (RI), but these interventions may be associated with additional risks in the young person and do not represent a cure because the patient is then dependent on lifelong levothyroxine replacement.^7 8^ Hence, there is a pressing need to develop interventions that can cure a disease that can have major lifelong implications.^8^

Modern immunomodulatory agents have the potential to ameliorate or ‘switch off’ the immune response to produce durable remission in patients with Graves’ hyperthyroidism. Rituximab (RTX), a chimeric anti-B cell monoclonal antibody (MAb) targeting the surface molecule CD20, leads to reductions in B lymphocyte populations lasting for around 6 months in more than 95% of people following one or two doses.^9^ CD20 is only expressed on pre-B lymphocytes and mature B cells; it is not expressed on B lymphocyte stem cells or the committed plasma cell. Circulating B lymphocytes are bound by the antibody and removed via antibody-dependent cellular cytotoxicity, complement-mediated lysis and apoptosis. RTX has been successfully used to treat B cell malignancies, with more than one million patients treated worldwide in recent years.^10^ It has also been used in a range of autoimmune disorders because of its favourable safety profile in adults and children.^11 12^

RTX has recognised disease-modifying activity both in people with organ-specific and non-organ specific immune-mediated disorders.^11–17^ B cell depletion with RTX has been shown to have disease-modifying effects in rheumatoid arthritis, systemic lupus erythematosus (SLE), autoimmune thrombocytopaenia, myasthenia gravis, and polyangiitis with granulomatosis including classical T-cell-mediated autoimmune diseases such as multiple sclerosis and type 1 diabetes. B cell depletion at sites of active inflammation reduces antigen presentation to autoreactive T lymphocytes, leading to amelioration of the cytotoxic autoimmune attack. While autoreactive B cells may return in some patients following RTX,^18^ the impact on disease outcome is not closely linked to circulating antibody levels, and the diverse function of B cells including their impact on T cell activity may explain why there may be an effect of RTX many years postadministration.^19–22^

B lymphocyte depleting immunotherapy appears to have disease-modifying activity in adults with Graves’ hyperthyroidism; RTX administration has been associated with encouraging remission rates, with approximately 50% of thyrotoxic adults in case reports and case series becoming euthyroid following treatment with RTX.^23–28^ Many of these patients were selected on the basis of more severe disease with relapsed Graves’ hyperthyroidism or aggressive orbitopathy. The management of cases where there was no clear response to RTX was characterised by early intervention with ATD, surgery or RI within the first year after RTX therapy, which may have obscured a beneficial effect of immunotherapy on thyroid status. Graves’ hyperthyroidism and Graves’ orbitopathy (GO) have several immunopathogenic features in common, including shared autoantigens, and several studies indicate that RTX has the potential to modify the natural history of thyroid eye disease.^29–31^ However, this has not been a consistent observation, with one randomised trial showing no impact of RTX on GO.^32^ The difference in trial outcome has been reviewed,^33^ and the differences could reflect factors such as the younger age of those recruited to the trial in Italy.^30^

RTX has an excellent safety record in the young and has been used extensively in paediatric practice to treat autoimmune cytopaenias, juvenile dermatomyositis, juvenile idiopathic arthritis, SLE and renal disorders, with significant side effects uncommon.^16 34^ Rates of infection appear to be low.^14^ Hypogammaglobulinaemia is a possible but very rare side effect in young people and may reflect an underlying but previously unrecognised immunodeficiency.^35^ The rare complication, progressive multifocal leucoencephalopathy, has been seen almost exclusively in adult patients with complex disorders who have received multiple immune suppressants (eg, those with B cell malignancies, multiorgan refractory SLE).

The aim of this clinical trial is to explore whether RTX administration will have a beneficial impact on the disease course in young people presenting with Graves’ hyperthyroidism. Specifically, we have set out to establish whether a single 500 mg dose of RTX, when administered together with a 12-month course of ATD, will increase remission rates in young people with Graves’ hyperthyroidism.

Previous treatment regimens in adults with Graves’ disease or GO have typically used between 1000 and 2000 mg RTX administered in divided doses. In contrast, a single dose of 500 mg RTX was used in a recent trial of patients with GO.^30^ The investigators in this trial subsequently reduced the dose of RTX to 100 mg in some of their trial patients because complete peripheral B cell depletion was still seen with this smaller dose. Our selection of 500 mg of RTX was a pragmatic decision bearing in mind the established efficacy in many disorders of 2×1000 mg doses versus the observation that a profound effect on B cell numbers was still observed with a much smaller dose. We were also keen to reduce the complexity associated with repeated visits to hospital for an intravenous infusion. By using a modest dose of 500 mg RTX on one occasion, we anticipated a meaningful effect on immune system function but a reduction in potential side effects.^27^

A course of ATD will be also prescribed in addition to a single dose of RTX so that patients are rendered clinically and biochemically euthyroid while the immune modulating effects of RTX alter the underlying immune disease process. A dose-titration ATD regimen will be used to reduce the likelihood of a subject having to stop ATD medication while still hyperthyroid.^36^ ATD will be stopped before 12 months has elapsed if patients become hypothyroid while on the smallest dose of ATD (5 mg CBZ alternate days). As well as preventing thyroid hormone production, ATD has a specific immunomodulatory effect, including reducing thyroid autoantibody concentrations during treatment.^37 38^ These effects may involve alteration of thyroid antigen structure,^2^ inhibition of proinflammatory cytokines or inhibition of T lymphocytes by other potential mechanisms.^39^ An additive or indeed synergistic effect of RTX and ATD is theoretically possible via combined effects on autoantibody generation, and the combination of RTX and ATD may increase remission rates above those observed in studies to date. Another advantage of the immunomodulatory approach to autoimmune hyperthyroidism is the potential for intervention to reduce the likelihood of longer term hypothyroidism.^40 41^

## Methods and analysis

### Trial objectives

The primary objective is to establish whether a single 500 mg dose of RTX, when administered together with a 12-month course of ATD, is likely to result in a meaningful improvement in the proportion of young people with Graves’ hyperthyroidism entering disease remission.

The secondary objectives are to examine (1) the relationship between thyrotropin receptor antibody (TRAb) titre and thyroid hormone status (thyroid stimulating hormone [TSH], free thyroxine [FT4] and free tri-iodothyronine [FT3]) in recruited subjects at the beginning and end of the trial; (2) whether immune cellular response is related to disease outcome by examining the relationship between time to recovery of B cell numbers measured in peripheral blood to within the local normal reference range and thyroid hormone status at the end of the trial; (3) whether total dose of ATD is related to disease outcome; (4) the time taken for TSH concentrations to normalise post-RTX and to describe thyroid status, as assessed by TSH, FT4 and FT3 concentrations (normal or abnormal), in the period between cessation of ATD therapy and the end of the trial in each patient; and (5) the safety of the trial treatment regimen by determining the nature and frequency of adverse events.

### Trial design

This is an investigator-initiated, open-label, single-arm, single-stage, phase II trial using an A’Hern design^42^ to determine whether the proposed new treatment is likely to meet a minimum level of efficacy before comparing it with standard treatment in a randomised trial. A single-arm design has been chosen because use of a control arm would require a much larger sample size resulting in a longer, more expensive trial when the potential benefit of RTX is, as yet, unknown. The design requires specification of the smallest remission rate, which if true would clearly imply that the treatment warrants further investigation, and the largest remission rate below which we would not wish to proceed to a larger definitive trial.

### Trial setting

This is a multicentre trial based in seven paediatric and seven adult tertiary endocrine units in the cities of Birmingham, Edinburgh, Newcastle, Leeds, Sheffield, Cardiff and Southampton UK and one secondary paediatric unit in Doncaster, UK.

### Inclusion criteria

Excess thyroid hormone concentrations at diagnosis: elevated free FT3 and/or FT4 (based on local assay).Suppressed (unrecordable) TSH (based on local assay).Patients between the ages of 12 and 20 years inclusive who are less than 6 weeks from the initiation of ATD treatment (CBZ or propylthiouracil [PTU]) for the first time.Elevated thyroid binding inhibitory immunoglobulin or thyroid receptor antibodies (TRAb including thyroid binding inhibiting immunoglobulin [TBII]) based on local assay. Patients may or may not have a raised thyroid peroxidase antibody titre.All patients must be willing to use effective forms of contraception for 12 months post-treatment with RTX.If women are of childbearing potential, they must have a negative pregnancy test at screening. This will need to be repeated on the day of RTX administration if more than 7 days has elapsed since the screening visit or a negative pregnancy test.Able and willing to adhere to a 2-year trial period.

### Exclusion criteria

Previous episodes of autoimmune thyroid disease.Patients with an active, severe infection (eg, tuberculosis, sepsis and opportunistic infections) or severely immunocompromised patients.Patients with known allergy or contraindication to CBZ and PTU.Participants with previous use of immunosuppressive or cytotoxic drugs (including RTX and methylprednisolone, but excluding inhaled glucocorticoid and oral glucocorticoid for asthma or topical glucocorticoid for eczema).Chromosomal disorders known to be associated with an increased risk of autoimmune thyroid disease, including Down’s syndrome and Turner syndrome.Pregnancy, planned pregnancy during the trial period or current breast feeding.Absence of informed consent from parent/legal guardian for participants age <16 years.Participants with significant chronic cardiac, respiratory or renal disorder or non-autoimmune liver disease.Participants with known allergy or contraindication to RTX or methylprednisolone.Participants with evidence of hepatitis B/C infection, assessed by determining hepatitis ‘B’ surface antigen (HBsAg) status, hepatitis ‘B’ Core antibody (HB Core antibody) status and hepatitis ‘C’ virus antibody (HCV antibody) status.Participants in families who know they will be moving out of the catchment areas during the 2 years following RTX treatment.Participants currently involved in any other clinical trial of an investigational medicinal product (IMP) or who have taken an IMP within 30 days prior to trial entry.

### Patient identification

Potentially eligible patients will be referred by their local clinician (general practitioner, paediatrician, physician or endocrinologist) or through self-referral via national organisations such as the British Thyroid Foundation (BTF) to a clinician with delegated responsibility to discuss the trial.

### Screening, recruitment and consent

Informed consent discussions will be undertaken by appropriate site staff, with an opportunity for the patient and the parent/guardian to ask questions. Following receipt of the patient information sheet (PIS), participants will be given a minimum of 24 hours to decide whether or not they would like to participate. As part of the consent discussions, the requirement to use effective contraception must be discussed. The PIS states that after the patient has given consent, they will be required to provide a blood sample and undergo a pregnancy test (if female) to confirm that they are not pregnant and that there is no evidence of hepatitis B/C infection. Some sites will also need to carry out HIV screening and QuantiFERON tests to confirm that the patients do not have tuberculosis and HIV (as per their local clinical policies) before a patient can be confirmed as eligible. Those wishing to take part will provide written informed consent/assent prior to trial-specific procedures/investigations. The information sheets and consent/assent forms are shown in online supplementary appendix 1 a, b,  c and d.

If thyroid antibody status (TRAb or TBII) was not determined at diagnosis, then this will be assessed at this consent and screening visit. The patient will be classified as a screen fail if they are found not to be eligible at this point. Ineligible patients will be notified via telephone and not asked to come in for a further trial visit. A screening log will be kept securely at each of the recruiting units (paediatric and adult units) to document details of eligible patients who have screen failed or declined to participate in the trial, including any reasons available. The right to refuse to participate without giving reasons will be respected.

### Intervention

RTX will be administered as a 500 mg dose by slow intravenous infusion under cover with methylprednisolone 125 mg intravenously, chlorpheniramine 10 mg intravenously, and 500 mg (12–16 years of age) or 1 g (>16 years) of paracetamol (orally). The RTX infusion will be started at a rate of 50 mg/hour, increasing by 50 mg/hour every half hour if tolerated; otherwise the infusion will either be maintained at the current rate or stopped and then restarted after 30 min. If the RTX infusion is tolerated and the rate increased as above, then the infusion will take 3.25 hours. Symptoms which are considered intolerable are angioedema, low blood pressure and difficulty breathing; if any are observed, the treatment will be stopped immediately, only to be restarted once symptoms have resolved. Vital signs including blood pressure will be measured every 30 min during the RTX infusion and for 2 hours afterwards.

RTX administered may only take place following confirmation that the patient is hepatitis B/C antibody-negative and within 7 days of a negative test for pregnancy (women). Administration of live vaccines is contraindicated or not recommended for at least 6 months following RTX administration.

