## Trial status

This manuscript is based on trial protocol V.4.0 dated 27 November 2017. The adjuvant rituximab, a potential treatment for the young patient with graves’ hyperthyroidism (RiGD) trial, opened to recruitment in October 2016 and is due to close to recruitment in October 2018.

10.1136/bmjopen-2018-024705.supp1Supplementary file 1

10.1136/bmjopen-2018-024705.supp2Supplementary file 2

10.1136/bmjopen-2018-024705.supp3Supplementary file 3

10.1136/bmjopen-2018-024705.supp4Supplementary file 4

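### The printed rituximab infusion steps deliver 500 mg in 2 h 55 min, ending at 300 mg/hour, not in the stated 3.25 hours

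*Protocol article*

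**What the plan says.** All the relevant text is in the Intervention section of the protocol article.

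- Dose: "RTX will be administered as a 500 mg dose by slow intravenous infusion".
- Starting rate: "The RTX infusion will be started at a rate of 50 mg/hour".
- Steps: "increasing by 50 mg/hour every half hour if tolerated". If an increase is not tolerated, the rate is held, or the infusion is stopped and restarted after 30 minutes.
- Stated result: "If the RTX infusion is tolerated and the rate increased as above, then the infusion will take 3.25 hours".
- Monitoring: "Vital signs including blood pressure will be measured every 30 min during the RTX infusion and for 2 hours afterwards".

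No maximum infusion rate appears in this section or anywhere else in the article. The Trial status section gives the source document: "This manuscript is based on trial protocol V.4.0 dated 27 November 2017". That full protocol is not at hand.

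**The concern.** The article prints a rule and also the duration that should follow from it. The dose, starting rate, increment and interval together fix how long a fully tolerated infusion takes, so the 3.25 hours can be checked directly. If it does not follow, either the duration is wrong or the rule lacks an element.

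What is at stake is the rate at which the later part of the dose is given to patients aged 12–20. The section treats rate as a tolerability control, since increases are conditional and intolerance means holding or stopping. Someone following the steps and someone working to the stated duration would end at different rates. The same ambiguity would pass to anyone reusing the regimen, including in the randomised trial that this study is meant to justify.

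**Working it through.** **Inputs (Intervention section).** Dose 500 mg; start 50 mg/hour; increment 50 mg/hour every 0.5 hour; stated duration 3.25 hours = 195 min. The stated duration applies when "If the RTX infusion is tolerated and the rate increased as above", so every increase is made and nothing is held or paused.

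**Formula.** In half-hour *k* the rate is 50*k* mg/hour, so the dose given in that half-hour is 50*k* × 0.5 = 25*k* mg. Sum until 500 mg is reached and prorate the last step.

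**The plan's own figure, from the printed rule.**

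| Time from start | Rate (mg/hour) | Dose in step (mg) | Cumulative (mg) |
|---|---|---|---|
| 0–30 min | 50 | 25 | 25 |
| 30–60 min | 100 | 50 | 75 |
| 60–90 min | 150 | 75 | 150 |
| 90–120 min | 200 | 100 | 250 |
| 120–150 min | 250 | 125 | 375 |
| 150–175 min | 300 | 125 | 500 |

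The last step takes 125 / 300 = 0.417 h = 25 min. The total is 150 + 25 = 175 min (2.92 h). The stated 195 min is not reproduced; the gap is 195 − 175 = 20 min.

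**What would give 3.25 hours?** Keeping the steps and adding a ceiling:

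| Ceiling (mg/hour) | Calculation | Duration |
|---|---|---|
| 150 | 150 mg at 1.5 h, then 350/150 = 2.33 h | 3.83 h |
| 200 | 250 mg at 2.0 h, then 250/200 = 1.25 h | **3.25 h** |
| 250 | 375 mg at 2.5 h, then 125/250 = 0.50 h | 3.00 h |
| 300 or none | 375 mg at 2.5 h, then 125/300 = 0.417 h | 2.92 h |

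Among ceilings, only 200 mg/hour matches, and it matches exactly.

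**Other readings.** A full first hour at 50 mg/hour gives 3.33 h, hourly steps 4.00 h, increments of 25 mg/hour 3.78 h, and one 30-minute pause 3.42 h. One other route reaches 3.25 h: holding the 100 mg/hour step for an extra half-hour. That gives 25 + 50 + 50 + 75 + 100 = 300 mg at 2.5 h, 125 mg more at 250 mg/hour by 3.0 h, and the last 75 mg at 300 mg/hour in 0.25 h. The condition quoted above excludes it, because a held step is not an increase made according to the rule.

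**Difference between the printed rule and the 200 mg/hour schedule.**

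- Final rate: 300 against 200 mg/hour.
- Dose given above 200 mg/hour on the printed rule: 125 mg (30 min at 250) + 125 mg (25 min at 300) = 250 mg in 55 min, which is 250/500 = 50% of the dose. On the capped schedule it is 0 mg.
- Dose delivered by 175 min: 500 mg on the printed rule; 250 + 200 × 55/60 = 433 mg with the ceiling.
- Up to 120 min the two schedules are identical.

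**The case against.** The strongest reply is that this is a detail lost in condensing. The stated duration is reproduced exactly by the same steps with a 200 mg/hour ceiling, which suggests that it was worked out from a fuller schedule and that one phrase was dropped. A maximum rate is the sort of administration detail that an article leaves to its full protocol, and V.4.0 may well state it. On that view the trial's actual dosing instruction may be entirely consistent.

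This is probably how the discrepancy arose, but it does not remove it. The defence covers what an article leaves out. Here the article prints both the rule and its numerical consequence, and they cannot both be right. If V.4.0 does contain a ceiling, the step rule as printed is incomplete in a way that changes the rate.

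A second objection has more force: 200 mg/hour is printed nowhere. It is inferred from the 3.25 hours, and nothing in the article says that faster rates are unsafe or unintended. The comparisons with 200 mg/hour therefore describe the gap between two readings, not a breach of a documented limit. The only discrepancy between printed figures is the 20 minutes.

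Third, the practical effect is small, and this stands. Increases are conditional on tolerance, premedication is given, the infusion stops for angioedema, low blood pressure or difficulty breathing, and vital signs are taken every 30 minutes. The analysis requires more than 100 mg to have been received; both schedules pass that amount between 60 and 90 minutes, before they diverge. No visit window, decision or endpoint depends on the 3.25 hours.

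**Conclusion.** The concern holds, as a minor point. The printed steps give 175 minutes and a final rate of 300 mg/hour; the stated duration is 195 minutes. The 20-minute gap is too large for rounding in a figure given to the quarter hour. The calculation assumes only what the sentence itself assumes: full tolerance, every increase made on time, no pause.

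An omitted 200 mg/hour maximum is the likeliest explanation, because it alone among ceilings reproduces 3.25 hours. That remains an inference, and the article does not settle whether the rule or the duration is wrong. If the ceiling was intended, following the printed rule gives half the dose faster than intended. There is no effect on the sample size, error rates, analysis population or primary analysis.

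**What to change.** Check the infusion instructions in full protocol V.4.0, then make one of two changes in the Intervention section:

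- If a ceiling is intended, add a maximum of 200 mg/hour to the step rule and keep 3.25 hours.
- If no ceiling is intended, keep the rule and correct the duration to about 2 h 55 min.

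The cost is one phrase or one number. If V.4.0 carries the same wording, it needs the same correction, and sites should be told which schedule applies.
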